## Background

Proximal femoral fracture, more commonly referred to as hip fracture, is a common, major health problem in old age [1], and as the population ages, the number of elderly people falling and fracturing their hips is projected to increase further. Occurrence of hip fracture is strongly associated with decreased bone mineral density, increased age, prior fragility fracture, low muscular strength levels, cognitive impairment, chronic disease, under-nutrition, frailty, poor physical functioning, vision problems and weight loss (especially muscle loss) [2]. Mortality is high with 25% dying within the following 12 months. A review of the long-term disability associated with proximal femoral fracture found that 29% of patients did not regain their pre-fracture level of functioning after 1 year in terms of restrictions of activities of daily living [3]. Many people who were living independently before their fracture lose their independence afterwards, so it imposes a large health and social care cost burden on society amounting to £2.3 billion a year in the UK, equating to approximately £6 million a day [4]. Tian et al. [5] explored Torbay’s (Devon) unique patient-level linked data set of National Health Service (NHS) and social care costs for older people in the 12 months before and after being admitted to hospital as a result of a fall. They found that the cost of hospital, community and social care cost services for each patient were almost four times as costly in the 12 months after admission, compared to the costs of the admission itself, and that the majority of costs occurred outside of the acute hospital setting. Particularly frail individuals may go onto have a further proximal femoral fracture resulting in additional disability and deaths [6].

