### Study objectives

The objectives of this study are the following:To assess the acceptability of, and compliance with, the rehabilitation programme amongst patients, carers and clinicians and the fidelity of its delivery and to identify any adverse events.To assess the feasibility of a future definitive RCT by assessing the number of eligible patients, monitoring recruitment and retention rates, exploring the willingness of patient participants to be randomised and the willingness of patients and carers to complete process and outcome measures.To produce means and standard deviations of the quantitative measures so that effect sizes can be calculated for planning the future RCT.To explore how the intervention creates change in self-efficacy and fear of falling as potential mediators for improving function.To explore the methodological issues for conducting an economic evaluation alongside a future RCT including identifying the most efficient way of measuring patient level costs and health benefits, programme costs and potential payer stakeholders.To explore the feasibility and quality of data on service use extracted from patient electronic records compared with patient reported outcome measures. If successful, replacing patient reported outcomes of service use with data collection by researchers and the NHS information technology (IT) staff for electronic records has potential to reduce participant burden in future studies (this is referred to as the triangulation study later in the paper).

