#### Health economic measures

EuroQol EQ-5D (three levels) [37].

This is a patient-completed index of health-related quality of life, which gives a weight to different health states. It consists of five dimensions: mobility, self-care, usual activities, pain/discomfort, and anxiety/depression. Each has three possible responses. The responses record three levels of severity (no problems, some/moderate problems and extreme problems) which is then converted to a health utility weight using UK norms. It will be used at baseline and at the 3-month follow-up assessment and allows the calculation of quality-adjusted life years (QALYs), using area under the curve method which will be used as part of the economic analysis.ICEpop CAPability measure for Older people [38,39].

This is a patient-completed measure of capability in older people that focuses on well-being rather than health. It comprises five attributes: attachment (love and friendship); security (thinking about the future without concern); role (doing things that make you feel valued); enjoyment (enjoyment and pleasure); and control (independence). Each attribute has four possible responses. The responses record the extent of capability (all, a lot, a little, and none), and the five-digit outcome is converted to capability utility derived from UK norms. It will be used at baseline and at the 3-month follow-up assessment as part of the economic analysis.Client service receipt inventory (CSRI) [40].

The CSRI is a questionnaire for collecting retrospective information about study participants’ use of health and social care services, including voluntary services (e.g. charity services), including the components of the rehabilitation programme. This information will be combined with national sources of reference unit costs [41,42] in order to calculate health and social care service costs for the economic evaluation. It will be used at baseline and at the 3-month follow-up assessment as part of the economic analysis.Discrete choice experiment [43,44].

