#### Economic analysis

The enhanced rehabilitation programme will be fully costed using unit costs from a public sector multiagency perspective. Unit costs will be obtained from national sources of reference costs [41,42] and applied to information received from pilot questionnaires, namely salary band of therapists, time spent with the patient conducting rehabilitation, costs of travel and costs of any additional equipment. Costs of health and social care services used by the participants will also be costed using national sources of reference costs. The costs of service use and the cost of the intervention will be added together for use in a cost-effectiveness analysis.

The EQ-5D (3L) will be used to calculate QALYs over the 3-month study period, using area under the curve method [56,57]. An exploratory cost-utility analysis will be conducted to calculate a cost per QALY of the enhanced rehabilitation intervention. This cost per QALY generated will be compared to the NICE threshold range of £20,000 to £30,000 per QALY [58]. If a treatment/intervention costs more than £20,000 to £30,000 per QALY, then it would not be considered cost effective.

The ICEpop CAPability measure for Older people (ICECAP-O) [59] will be used to calculate a capability index score. An exploratory cost-effectiveness analysis will be conducted to calculate a cost per unit change in ICECAP-O score. We will compare the use of these two approaches, cost-utility analysis using QALYs and cost-effectiveness analysis using ICECAP-O, as a capability measure. We will explore the extent to which they can help guide commissioning decisions following a full trial and full economic evaluation.

The FEMuR feasibility study includes a discrete choice experiment [43,44] to look at the participant’s preferences for the ‘process’ of exercise programmes. The discrete choice experiment will assess which attributes are important to participants and will be administered at the 3-month follow-up. Based upon the data received from the feasibility study, we will assess whether the use of a discrete choice experiment is possible from a full scale RCT of the FEMuR multidisciplinary rehabilitation.

Finally, we will scope out the potential of conducting a social return on investment (SROI) analysis based on the data obtained from the feasibility study to inform whether a full SROI analysis is possible from a full-scale RCT of the FEMuR multidisciplinary rehabilitation intervention [60].

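### A cost per QALY over 3 months from about 50 patients is read against the £20,000–30,000 NICE range with no caveat on horizon or uncertainty, and cannot support that verdict

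*Protocol article*

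**What the plan says.** In the protocol article, the Economic analysis section costs the enhanced programme in full and adds the cost of health and social care used. On benefit it says: "The EQ-5D (3L) will be used to calculate QALYs over the 3-month study period, using area under the curve method". Table 1 and the Health economic measures section place EQ-5D at baseline and 3 months, with no other assessment.

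The status of the analysis is given as follows: "An exploratory cost-utility analysis will be conducted to calculate a cost per QALY of the enhanced rehabilitation intervention". The next sentences read: "This cost per QALY generated will be compared to the NICE threshold range of £20,000 to £30,000 per QALY", and then: "If a treatment/intervention costs more than £20,000 to £30,000 per QALY, then it would not be considered cost effective". Neither sentence mentions the 3-month horizon or sampling uncertainty.

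Three other statements bear on how this should be read:

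- The relevant aim under Study objectives is "To explore the methodological issues for conducting an economic evaluation alongside a future RCT".
- Later in the Economic analysis section, the use of QALYs and ICECAP-O for commissioning is placed after a full trial.
- The feasibility criteria in the Statistical analysis and Discussion sections concern eligibility, recruitment and retention. None uses the cost per QALY.

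**The concern.** The article fixes a horizon and also gives a verdict rule, and the two do not fit together. A ratio of cost to QALYs depends on how long both are counted. The six extra sessions are logged in Table 1 within the 3 months, so most or all of the programme cost probably falls inside the window. Any gain in function or independence that lasts longer is not counted.

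The Background treats recovery as a longer process: 29% of patients had not regained their former function after 1 year, and care costs are described over 12 months after admission.

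If the text were followed literally, the study could report that enhanced rehabilitation fails the NICE range when the result reflects the length of follow-up. About 50 patients are randomised 1:1, so the ratio would also be imprecise. For the Barthel index, the Statistical analysis section itself says that an accurate description of group differences would need a larger sample. The cost per QALY carries no similar caution. Readers and funders of the definitive trial could be misled.

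**Working it through.** The article states no cost per QALY, programme cost or EQ-5D effect, so there is no plan figure to reproduce. The question is how far the ratio depends on the horizon.

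**Inputs from the article:** horizon 3 months (0.25 year); EQ-5D at two time points; area under the curve; range £20,000 to £30,000 per QALY.

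**Assumptions (not in the article):** equal baseline utility in the arms; a between-arm utility difference *d* at 3 months, taken as 0.05 or 0.10; incremental cost *C* of £150 to £800 per patient; after 3 months the difference ends, wanes linearly to zero at 12 months, or is held to 12 months with deaths ignored.

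**Step 1. QALY gain at 3 months.** Two points define a triangle: 0.5 × 0.25 × *d* = 0.125*d*.

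**Step 2. QALY gain at 12 months.**
- Ends at 3 months: 0.125*d*.
- Wanes to zero: 0.125*d* + 0.5 × 0.75 × *d* = 0.50*d*.
- Held: 0.125*d* + 0.75*d* = 0.875*d*.

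**Step 3. Ratio of the 3-month to the 12-month cost per QALY at equal incremental cost.**
- Ends: 0.125/0.125 = 1.
- Wanes: 0.50/0.125 = 4.
- Held: 0.875/0.125 = 7.

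**Step 4. Cost per QALY under a range of assumptions (*C* divided by the gain).**

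| *C* | *d* | 3 months | 12 months, waning | 12 months, held |
|---|---|---|---|---|
| £150 | 0.10 | £12,000 | £3,000 | £1,714 |
| £300 | 0.05 | £48,000 | £12,000 | £6,857 |
| £500 | 0.10 | £40,000 | £10,000 | £5,714 |
| £800 | 0.05 | £128,000 | £32,000 | £18,286 |

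In the second and third rows the reading moves from above the range to below it on horizon alone. In the first row it is below the range throughout. In the fourth it is above at 3 months, still above if the gain wanes, and below if it is held.

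**Step 5. What would cancel the shift.** Let *L* be the extra service cost per patient in the intervention arm between 3 and 12 months, and *k* the ratio from Step 3. The two horizons agree when (*C* + *L*)/(*k* × 0.125*d*) = *C*/(0.125*d*), so *L* = (*k* − 1)*C*. That is 3*C* if waning and 6*C* if held. With *C* = £500, this is £1,500 or £3,000. Later savings (negative *L*) would widen the gap.

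**The case against.** The strongest reply is that the article does not commit the study to a verdict. The sentence about the threshold is worded for any treatment and explains how the NICE range is commonly read. The study's own commitment is an exploratory analysis whose result is compared with the range. Commissioning is deferred to a later trial, and the progression criteria do not touch the economic result. Rehearsing the whole calculation, benchmark included, is a fair task for a feasibility study. This stands, and it limits the consequence. It does not make a 3-month ratio interpretable at the threshold, and a comparison followed directly by the rule invites that reading.

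A reader might go further and infer that the plan is biased towards finding the programme not cost effective. The article does not support that:

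- Such a bias needs a benefit that outlasts 3 months and later costs that do not offset it. The article gives neither.
- Service costs and savings after 3 months are cut off along with benefit.
- It is not stated that the whole programme cost falls inside the window. Sessions are used according to need, and no end date is given.
- The Interventions section aims at function at the 3-month follow-up, so the article does not show that benefit is only beginning then.
- The Background remark that "the majority of costs occurred outside of the acute hospital setting" concerns where costs fall, not when, and comes from admissions after falls.

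The factor of 7 also ignores deaths, although the Background puts mortality at 25% within 12 months. It should be read as the outcome of a favourable assumption.

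**Conclusion.** The point holds in a conditional form and is minor. A 3-month cost per QALY from about 50 patients cannot support a reading against £20,000–30,000, and the article attaches that reading without a caveat. It goes beyond the methodological objective that the article sets for the economic work.

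The possible distortion is a factor of 4 (waning) to 7 (held, no deaths) relative to 12 months. This rests on equal baselines, equal incremental cost at both horizons and a benefit that continues after 3 months. There is no distortion if the benefit ends at 3 months, and large enough later service costs would remove it. A definite bias against the intervention therefore cannot be claimed. What can be claimed is that the reading may change with the horizon alone, and that the article gives no means of telling whether it would. No decision to proceed depends on the figure, which keeps the severity low.

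**What to change.** - Keep the 3-month cost-utility result and describe it as exploratory and descriptive.
- Remove the threshold reading for this study, or state that it does not apply at a 3-month horizon.
- Report incremental cost and incremental QALYs with confidence intervals, labelled as 3-month.
- As a labelled scenario only, show the result with the 3-month utility difference ending, waning to zero, or persisting to 12 months, and use it to choose the horizon of the definitive evaluation.

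This costs a change of wording and a short calculation on data already being collected. The drawbacks are that the feasibility study gives up a headline cost-effectiveness statement, and that the scenarios carry an imprecise difference forward on assumptions it cannot test.

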#### Randomisation

Patient participants who give their informed consent will complete baseline process and outcome measures before being individually randomised. The randomisation will be performed by dynamic allocation [21] to protect against subversion whilst ensuring that the trial maintains good balance to the allocation ratio of 1:1 both within each stratification variable and across the trial. Participants will be stratified by: (1) hospital and (2) gender.

Randomisation will be requested by the researcher who has taken informed consent and will be achieved by secure web access to the remote randomisation centre at the North Wales Organisation for Randomisation Trials in Health (NWORTH), Bangor University. This system will be set up, maintained and monitored independently of the trial statistician or other trial staff. The randomisation procedures will be aligned with NWORTH standard operating procedure 5.01 to ensure best practice. The key to the randomisation code will be held centrally by NWORTH.

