#### Statistics

##### Sample size

We estimate that we will recruit 25% of eligible patients with a proximal femoral fracture admitted to the three acute hospitals in BCUHB and randomise them to either the enhanced rehabilitation programme or usual care. In order to estimate the standard deviation of the primary outcome measure (Barthel index), which will be used in a power calculation for a future definitive RCT, with a high level of confidence a sample size of at least 50 participants completing the trial is advisable [55].

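### The cost-per-QALY threshold is a valid criterion only when the QALY difference is positive, and in a trial of about 50 patients its estimate may well be negative

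*Protocol article*

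**What the plan says.** All of this is in the protocol article, mainly under Economic analysis.

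- Numerator: "The costs of service use and the cost of the intervention will be added together for use in a cost-effectiveness analysis".
- Denominator: "The EQ-5D (3L) will be used to calculate QALYs over the 3-month study period, using area under the curve method".
- Status of the ratio: "An exploratory cost-utility analysis will be conducted to calculate a cost per QALY of the enhanced rehabilitation intervention".
- Comparison: "This cost per QALY generated will be compared to the NICE threshold range of £20,000 to £30,000 per QALY".
- Verdict: "If a treatment/intervention costs more than £20,000 to £30,000 per QALY, then it would not be considered cost effective".
- A second ratio, with no threshold attached: "An exploratory cost-effectiveness analysis will be conducted to calculate a cost per unit change in ICECAP-O score".

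The section does not mention the sign of either difference, dominance, net benefit or uncertainty in the ratio. On size, the Sample size section says that "a sample size of at least 50 participants completing the trial is advisable", and Randomisation specifies an "allocation ratio of 1:1".

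**The concern.** A ratio of a cost difference to a QALY difference ranks results by value for money only while the denominator stays positive. Once the denominator can be negative, one value of the ratio can describe opposite situations, and a comparison with an upper limit no longer means what it appears to mean. In a study of about 50 patients followed for 3 months, a negative estimated QALY difference is an ordinary outcome even if the programme does no harm.

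Two things are at stake: how the exploratory cost-utility result is read, and whether a point ratio with a threshold is carried into the full trial. The second matters because Study objectives makes exploring economic-evaluation methods for that trial one of the study's purposes.

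**Working it through.** **Inputs.** From the documents: thresholds λ of £20,000 and £30,000 per QALY (Economic analysis); 50 completers at 1:1, so 25 per arm (Sample size, Randomisation); 75% retention as a sensitivity check, 0.75 × 50 = 37.5, or about 19 per arm (Discussion). The ratio is taken as incremental, dC/dQ, enhanced minus usual care. The documents give no QALY SD, cost difference, cost SD or cost-QALY correlation, so every value used for these below is an assumption. The plan states no error rate for this criterion, so there is no figure of its own to reproduce.

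**Step 1: algebra.** Net monetary benefit is NMB = λ × dQ - dC.

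- If dQ > 0, then dC/dQ > λ means dC > λ × dQ, so NMB < 0. The criterion agrees with net benefit.
- If dQ < 0, multiplying through by dQ reverses the inequality: dC/dQ > λ means dC < λ × dQ, so NMB > 0. The criterion runs opposite to net benefit.

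**Step 2: sign cases.**

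| dC | dQ | dC/dQ | Above threshold? | NMB at £20,000 | NMB at £30,000 |
|---|---|---|---|---|---|
| +£600 | -0.01 | -£60,000 | No | -200 - 600 = -£800 | -300 - 600 = -£900 |
| -£600 | +0.01 | -£60,000 | No | 200 + 600 = +£800 | 300 + 600 = +£900 |
| -£600 | -0.01 | +£60,000 | Yes | -200 + 600 = +£400 | -300 + 600 = +£300 |

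Rows 1 and 2 share one ratio but are the worst and best kinds of result. Row 3 is above the threshold although its net benefit is positive.

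**Step 3: how often.** If the true QALY difference is 0 and its estimate is symmetric, P(dQ < 0) = 0.50. By Step 1 the literal criterion and net benefit disagree exactly when dQ < 0, so they disagree in half of such trials. This needs no SD, cost, sample size or correlation.

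**Step 4: how often the ratio is not above the threshold.** With a fixed positive dC and a true QALY difference of 0:

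P(not above) = 0.5 + [1 - Φ(dC/(λ × SE))], where SE = SD × √(2/n).

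For an assumed QALY SD of 0.04, dC of £500 and n = 25, SE = 0.04 × √(2/25) = 0.0113.

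- At £20,000: 0.0250/0.0113 = 2.21, upper tail 1.4%, so 51.4%. Net benefit is positive in 1.4%.
- At £30,000: 0.0167/0.0113 = 1.47, upper tail 7.0%, so 57.0%. Net benefit is positive in 7.0%.

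Over assumed QALY SDs of 0.02 to 0.08 and dC of £200 to £2,000, the ratio is not above the threshold in 50.0% to 88.4% of trials (50.0% to 89.9% with 19 per arm). Net benefit is positive in 0.0% to 38.4% with 25 per arm. With a true loss of 0.01 QALY (SD 0.04, dC £500, 25 per arm), the ratio is not above the threshold in 81% to 82%.

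**Step 5: random cost difference.** Simulated with 25 per arm, true QALY difference 0, assumed mean extra cost £0 to £2,000 and cost SD £1,000 to £6,000. With independent cost and QALY estimates, the ratio is not above the threshold in about 50% to 87%. With a cost-QALY correlation of +0.3 or +0.5, the minimum falls to 42% or 35%. The one-half disagreement in Step 3 does not change.

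**The case against.** The strongest reply is that the sentence gives one reason for calling an intervention not cost effective. It never says that every other ratio, negative ones included, will be called cost effective. That stands. A reader might infer that the plan would endorse a harmful, costlier programme, but the text does not say so. What remains is that this is the only criterion stated, and it gives no usable answer when dQ is negative.

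A reader might also infer that an ineffective programme would escape rejection more than half the time. That is not general. It needs an effectively certain extra cost, or cost and QALY estimates that are not positively correlated. Even then the excess over one half can be negligible.

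Three further replies have some force.

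- The section does not use the word incremental. An average cost per QALY in one arm would not turn negative in this way. But the study compares enhanced with usual care, and an average would not measure what the enhanced programme adds.
- Statistical analysis promises descriptive results for all outcome measures and intervals for the secondary ones, so the direction of the EQ-5D difference should be partly visible. The verdict on value for money is still tied to the ratio.
- Dominance and bootstrap methods often sit in a fuller protocol or health economics plan. Their absence from an article is no fault. The point here concerns the criterion that the article does state.

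**Conclusion.** The point holds in a limited form. Read as an incremental ratio, the stated criterion is sound only for a positive QALY difference. At a true difference of zero it runs opposite to net benefit in half of trials. That result rests on the algebra, a symmetric estimate and a literal reading of the criterion. The percentages in Steps 4 and 5 rest on assumed SDs, costs and correlations.

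The consequence is modest. The cost-utility analysis is labelled exploratory, and the feasibility criteria in Statistical analysis and Discussion are eligibility, recruitment and retention only. Nor do the documents support saying that this result will itself guide commissioning: the article will explore how far the two approaches could do so after a full trial and full economic evaluation. For ICECAP-O no threshold or verdict is set, so the faulty comparison does not arise there. Only the ambiguity of a ratio with a denominator of either sign carries over.

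**What to change.** In Economic analysis:

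1. Report the cost difference and the QALY difference separately.
2. Judge against the threshold by incremental net monetary benefit at £20,000 and at £30,000 (threshold × QALY difference - cost difference), each with a bootstrap 95% interval. Resample patients within arm so that each patient's cost and QALY stay paired.
3. Quote a cost per QALY only when both differences are positive. Otherwise say in words whether the programme dominates, is dominated, or saves cost at a loss of QALYs.
4. For ICECAP-O, give the cost and score differences alongside any ratio.

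This costs some wording and a short bootstrap on data already collected, with no new patients or measurements. The drawback is that the headline becomes an interval that will probably span zero. As an illustration, assume a QALY SD of 0.04, a cost SD of £3,000, no correlation and 25 per arm. At £20,000 the SE of net benefit is √[(20,000 × 0.04 × √(2/25))² + (3,000 × √(2/25))²] = √(51,200 + 720,000) = £878, so the 95% interval is about ±£1,720. That width is a fair picture of what a study of this size can say about value for money.
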